#### Time From Injection to Fluorescence Imaging

The time from injection of indocyanine green dye to fluorescence imaging will be recorded. We predict that there will be a minimum of two groups of patients for analysis of the results of fluorescence imaging in view of the variability of operation durations associated with the procedure (eg, <180 minutes versus >180 minutes). Patients with prolonged operative procedures and complete clearance of indocyanine green dye from the operative specimen will be excluded from further analysis. The limit of the timing for fluorescence imaging after indocyanine green injection has yet to be determined.

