## Methods

### Study Design

The SeLyNoFI study is designed as a single-arm, 2-step (monomulticentric), academic, prospective observational-interventional study conducted by the Department of Surgical Oncology at the Institute Jules Bordet of the *Université Libre de Bruxelles* in Brussels. It will start as a monocentric, 2-stage (Simon procedure) study and will be followed by a multicentric study (among members of the International Research Institutes network) if the null hypothesis that the sensitivity of the indocyanine green–fluorescence imaging technique is lower than 60% (*p*_0_, sensitivity obtained by the classical blue dye technique improved by 10%) can be rejected based on the data generated in the monocentric study (*p*_1_, power calculated in case of a true sensitivity of 90%). To assess the feasibility of this technique, all cases will be included, even under conditions in which the technique might be expected to be unreliable (eg, long delay between injection of indocyanine green dye and fluorescence assessment). However, if the null hypothesis cannot be rejected after the monocentric phase, further development will be halted (Figure 2).

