### Statistical Analyses

The sensitivity of the first step (monocentric study) will be evaluated for patients where the fluorescence evaluation has been performed just after the colectomy in the operating room and also afterward in the pathology department.

Sensitivity and positive predictive value will be computed at the patient level, on the total, and in different subgroups based on histology of the tumor (nonmucinous versus mucinous adenocarcinoma) or delay between injection of indocyanine green dye and fluorescence examination.

Upgrading percentage will be calculated on fluorescent lymph nodes with negative pathological examination. Concordance between visual scale and tumor-to-background fluorescence ratio will be evaluated with the kappa statistic.

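### Excluding patients with complete dye clearance contradicts the all-cases rule and inflates reported sensitivity; the go/no-go error rate rises only if those patients are replaced

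*Protocol article*

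**What the plan says.** Three sections of the protocol article bear on this.

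- **Study Design.** To assess feasibility, "all cases will be included, even under conditions in which the technique might be expected to be unreliable". The example given is a "long delay between injection of indocyanine green dye and fluorescence assessment". The null hypothesis to be rejected is that "the sensitivity of the indocyanine green–fluorescence imaging technique is lower than 60" per cent.
- **Time From Injection to Fluorescence Imaging.** At least two delay groups are expected ("eg, <180 minutes versus >180 minutes"). Then: "Patients with prolonged operative procedures and complete clearance of indocyanine green dye from the operative specimen will be excluded from further analysis". And: "The limit of the timing for fluorescence imaging after indocyanine green injection has yet to be determined".
- **Statistical Analyses.** Patient-level sensitivity and positive predictive value are to be computed on the total and in subgroups, one of them defined by "delay between injection of indocyanine green dye and fluorescence examination".

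The Population section (first step) sets the go/no-go rule as a count of true positives among node-positive patients. It does not say whether a patient excluded from analysis is replaced.

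**The concern.** The condition that Study Design names as a reason to keep a case is the setting in which the later section removes it. The removal is not triggered by a long operation alone. It also needs the dye to be seen to have gone, which is learned from the imaging under evaluation. A node-positive patient whose specimen shows no dye cannot be a true positive. If kept, that patient counts as a miss. If dropped, the miss leaves the denominator. Because the time limit is undetermined, what counts as prolonged can be settled after the images have been seen.

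Patient-level sensitivity is the quantity on which the technique either moves to the multicentre step or is abandoned.

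**Working it through.** **Inputs.** From Study Design and Population: p0 = 0.60, p1 = 0.90, α = .05, β = .10, n1 = 8, r1 = 5 (to be surpassed), n_tot = 17 node-positive patients, r_tot = 14, node-positive prevalence 50%. Assumed, because the documents do not give it: c, the share of node-positive patients excluded for complete clearance, at 5%, 10% and 20%.

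**1. Reproduce the design.** The chance of passing at sensitivity p, with success at k or more of 17, is

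P(p) = Σ over x = 6, 7, 8 of Pr[Bin(8, p) = x] × Pr[Bin(9, p) ≥ k − x].

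For k = 14 and p = 0.60: 0.2090 × 0.0705 + 0.0896 × 0.2318 + 0.0168 × 0.4826 = 0.0436. At p = 0.90 the result is 0.9045. The stated α and β are therefore met with success at 14 or more, and 17/0.50 = 34 enrolled. The text asks for the total to surpass 14. Read literally (k = 15), that gives α = 0.012 and power 0.762. This mismatch is a separate matter, so both readings are carried below.

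**2. Effect on the estimate.** Let s be the all-case sensitivity, TP/N, with N the number of node-positive patients. Dropping cN patients who are all misses gives TP/(N − cN) = s/(1 − c). At s = 0.60: 0.60/0.95 = 0.632, 0.60/0.90 = 0.667, 0.60/0.80 = 0.750.

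**3. Effect on the false-go rate if excluded patients are replaced** until 17 analysable node-positive patients are reached. Put s/(1 − c) into P. For c = 10%, k = 14: 0.2731 × 0.1431 + 0.1561 × 0.3772 + 0.0390 × 0.6503 = 0.123.

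| c | Apparent sensitivity when all-case is 60% | False-go, ≥14/17 | False-go, ≥15/17 |
|---|---|---|---|
| 0 | 60.0% | 4.4% | 1.2% |
| 5% | 63.2% | 7.3% | 2.3% |
| 10% | 66.7% | 12.3% | 4.4% |
| 20% | 75.0% | 33.7% | 16.4% |

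**4. Without replacement.** The rule counts true positives. A dropped miss adds nothing to that count, just as a retained miss adds nothing. Among 17 node-positive patients the count is still Bin(17, 0.60), with the same stage 1 stop, so the false-go rate stays at 4.4% (or 1.2%). The reported proportion still moves: 13 of 17 is 76.5%, but with two cleared patients dropped it becomes 13 of 15, or 86.7%.

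**5. Other measures.** The exclusion is not limited to node-positive patients. A cleared node-negative patient would be a true negative if kept. If a share d of node-negative patients is dropped, an all-case specificity t becomes (t − d)/(1 − d), which is lower whenever t is below 1. Accuracy loses misses and true negatives together, so it can move either way. Positive predictive value is unaffected, because cleared patients are never test positive.

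**6. Effect of keeping all cases on the chance of passing.** If 90% is the sensitivity in retained patients, the all-case value is 0.90 × (1 − c).

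| c | All-case sensitivity | Pass, ≥14/17 | Pass, ≥15/17 |
|---|---|---|---|
| 0 | 90% | 0.905 | 0.762 |
| 10% | 81% | 0.571 | 0.347 |
| 20% | 72% | 0.244 | 0.106 |

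**The case against.** **The two sentences could be about different things**, enrolment in one and analysis in the other. This does not reconcile them. Study Design includes all cases in order to assess feasibility, which requires analysing them, and Statistical Analyses computes sensitivity on the total. No section says that cleared cases stay in the primary sensitivity.

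**Complete clearance may be a non-evaluable result rather than a negative one.** It describes the whole specimen, whereas an ordinary negative may be a fluorescent specimen without bright nodes. The distinction is fair, and scoring clearance as negative is an analysis choice that has to be argued. The argument is the protocol's own: the question is feasibility, and unreliable conditions are deliberately kept in.

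**The go rule is a count.** A reader might infer that the exclusion by itself breaks the Simon error rate. The documents do not support that. The inflation needs replacement, on which they are silent, and step 4 shows none without it. Even with replacement, the literal rule of more than 14 keeps the false-go rate below 5% up to c = 10%.

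**The size is unknown.** The documents give no value for c, and exclusion needs both a prolonged procedure and complete clearance. This stands, so the figures are a range and not a forecast.

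**Delay is already an analysis factor.** True, but a subgroup analysis by delay does not restore patients removed beforehand.

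**Conclusion.** The contradiction is real, and the direction of the bias in sensitivity is certain whenever a node-positive patient is excluded: upward, by 1/(1 − c). An all-case 60% would read as 63% to 75% for assumed c from 5% to 20%. This rests only on a fully cleared specimen being unable to yield a true positive.

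The effect on the go/no-go decision is conditional. With replacement to 17 node-positive patients, the false-go rate at 60% rises to between 7.3% and 33.7% over that range (success at 14 or more), or to between 2.3% and 16.4% (15 or more). Without replacement it is unchanged.

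A reader might also infer that the rule deletes nothing but false negatives. That is so only among node-positive patients. Cleared node-negative patients are dropped too, which lowers specificity and distorts accuracy.

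The point should be settled before recruitment, because a result-dependent exclusion with an open time limit cannot be repaired credibly once the images have been seen.

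**What to change.** Reconcile the section on time from injection to imaging with Study Design:

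- Keep every patient who received the dye and was imaged in the primary analysis and in the Simon count, with complete clearance scored as test negative whatever the nodal status.
- Report sensitivity by recorded injection-to-imaging delay, as Statistical Analyses already plans. The 180-minute split is only an example in the protocol and need not become the fixed cut.
- Allow an analysis restricted to evaluable specimens as secondary only, with its definition fixed in advance and the number excluded reported.
- State that p1 = 90% refers to all cases.

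The change takes a few sentences and no extra patients: 17 node-positive and about 34 enrolled remain. At an all-case sensitivity of 60%, α stays at 0.044 (14 or more). The cost may not be small. If clearance is common, both the estimate and the chance of passing fall. With 90% sensitivity in retained patients only, the chance of at least 14 of 17 drops from 0.90 to 0.57 at c = 10%. The sponsor therefore has to decide which population its 90% describes.

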#### Standard Sentinel Lymph Node Detection (Blue Dye Technique)

After fluorescence imaging in the operating room, a submucosal injection of 0.5 mL of patent blue dye will be injected at the 4 cardinal points around the primary tumor, and the injected area will be gently massaged to increase diffusion of the blue dye. After a few minutes, the mesentery will be explored for blue sentinel lymph nodes. Sentinel lymph nodes will be marked with a blue stitch.

### In the Pathology Department

#### Fluorescence Imaging

The operative specimen will be fixed and will be examined 24 hours later using standard methods for lymph node detection. Lymph nodes marked with a blue (blue sentinel lymph node) or green (fluorescent lymph node) stitch in the operating room will be examined separately and noted as blue or fluorescent lymph nodes. Concomitant blue and fluorescent lymph nodes will be noted as concordant sentinel lymph nodes for the two techniques.

Thereafter, nonstitch sentinel lymph nodes will be placed into cassettes and systematically examined for their blue or fluorescent staining and noted as fluorescent, blue, or neither blue nor fluorescent. Importantly, those stained lymph nodes found to be blue or fluorescent afterwards will not be classified as sentinel lymph nodes.

Finally, the operative specimen will be examined with the camera for complementary exploration and to evaluate whether fluorescence imaging is able to detect more lymph nodes than classical analyses can detect. Those lymph nodes will be categorized as *clinically unfound lymph nodes*.

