**Figure 1 figure1:**
[figure not shown]
Illustrations of the systemic sentinel lymph node hypotheses. In patients with small tumors, we expect to find a correlation between the blue sentinel lymph node and the systemic lymph node. In patients with large tumors, we expected to have a false negative blue sentinel lymph node and a true positive systemic lymph node. FI: fluorescence imaging; ICG: indocyanine green.

The primary objective of the SeLyNoFI study is to assess the feasibility of metastatic lymph node detection in colorectal cancer by ex vivo fluorescence imaging after intravenous administration of indocyanine green dye. In this study, we will evaluate the sensitivity, specificity, and accuracy of the technique for determining nodal status, both intraoperatively (entire fresh specimen imaging) and in the pathology department (fixed specimens).

The secondary objectives are to correlate the results of the fluorescent sentinel lymph node detection technique after intravenous injection of indocyanine green dye with sentinel lymph node detection by the standard blue dye technique, to study the link between the local lymphatic drainage pathway (classical tumor-draining sentinel lymph nodes) and the systemic pathway (systemic sentinel lymph nodes). Finally, we will evaluate the tumor-to-background fluorescence ratio of the primary colonic tumor.

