### In the Operating Room

#### Fluorescence Imaging

After colonic and rectal resection (as necessary), the operative specimen will be placed on a back table and the mesentery exposed. Fluorescence imaging is carried out with a dedicated near-infrared camera system. A light-emitting diode light source set to a wavelength of 760 nm is used, and the detector is a charge-coupled device (CCD) camera with a filter set to detect light with a wavelength of <820 nm. The fluorescent signal is sent to a digital video processor to be displayed on a monitor in real time. Videos will be recorded on a personal computer using a standard high-definition video program. The camera will be held directly by the surgeon at a distance of approximately 20 cm from the operative specimen. During fluorescence imaging exploration, hyperfluorescent lymph nodes will be marked with a green stitch. Thereafter, the colon will be opened, and primary tumors will be imaged for their fluorescence.

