## Discussion

Accurate nodal staging is crucial in colorectal cancer as a prognostic factor and to determine the need for adjuvant treatment. In patients with nodal invasion (stage III), adjuvant chemotherapy is required, while the benefit of adjuvant chemotherapy in stage II remains controversial [2]. Notably, 20% of patients identified as stage II colorectal cancer will experience recurrence, potentially due to missed lymph node metastases [2], justifying efforts to increase the accuracy of nodal staging. It has been clearly demonstrated that one of the most important prognostic factors associated with the accuracy of nodal staging is the number of lymph nodes analyzed from the operative specimen [22], and the Union for International Cancer Control recommends that at least 12 lymph nodes should be resected and analyzed [23]. In the early 2000s, sentinel lymph node detection in colorectal cancer emerged as a promising technique for increasing the accuracy of nodal staging, focusing pathological analyses on detection of micrometastases in a limited number of lymph nodes using advanced techniques such as serial section, immunochemistry, and reverse transcription polymerase chain reaction techniques [6]. Currently, however, the contribution of classical sentinel lymph node detection with blue dye in colorectal cancer remains a subject of debate [5,7,8]. One of the major limitations of this technique that uses intra- or peritumoral marker injection is that it may result in false negatives due to the fact that lymphatic drainage can be impaired by tumor compression in large tumors (pT3 and pT4) [5]. Therefore, the technique is mostly used for staging smaller tumors. This is inconsistent with the higher risk for nodal dissemination associated with large tumors compared to small tumors. Recently, the use of fluorescence imaging in the detection of sentinel lymph nodes has emerged as a promising technique in several cancers [9,11-16], but the sensitivity of the blue dye method in patients with stage pT3 or pT4 tumors remains disappointing [16]. This provides the rationale for finding a solution that overcomes this problem, such as using intravenous injection as we recently reported in a proof-of-concept study in metastatic colorectal cancer [17,18].

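### The final camera pass has no unaided second look beside it, so it can show additional yield but not that fluorescence finds more nodes than classical search

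*Protocol article*

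**What the plan says.** The order of work is fixed in the protocol article, Methods, In the Pathology Department, Fluorescence Imaging. The classical search comes first: "The operative specimen will be fixed and will be examined 24 hours later using standard methods for lymph node detection". Stitched nodes are examined separately. Unstitched nodes go into cassettes and are scored as fluorescent, blue or neither. The camera pass is the closing step: "Finally, the operative specimen will be examined with the camera for complementary exploration". Its aim is "to evaluate whether fluorescence imaging is able to detect more lymph nodes than classical analyses can detect", and nodes found then are labelled clinically unfound.

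Three other places bear on the point:

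- In the Operating Room, Fluorescence Imaging, describes an earlier fluorescence pass on the fresh specimen: "During fluorescence imaging exploration, hyperfluorescent lymph nodes will be marked with a green stitch".
- The primary objective, at the end of the Introduction, is to "assess the feasibility of metastatic lymph node detection in colorectal cancer by ex vivo fluorescence imaging after intravenous administration of indocyanine green dye". Neither it nor the secondary objectives name node yield against classical search.
- Statistical Analyses states "Sensitivity and positive predictive value will be computed at the patient level, on the total, and in different subgroups". It gives no test, threshold or other analysis for the extra nodes.

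**The concern.** Whether one method detects more than another is a comparison of methods. What the last pass records is how many nodes are added once the classical search has finished. Two things can produce such a node: the fluorescent signal, or simply looking again at the same fat. The section describes no unaided second search, so the count cannot tell them apart.

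The protocol guards against a similar problem elsewhere. Under Pathology Examination it recognises that unequal effort could bias micrometastasis detection towards fluorescent nodes, and has a similar number of negative nodes serially sectioned in the same way. Node retrieval has no such control.

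At stake is what may be claimed. The Discussion puts it this way: "one of the most important prognostic factors associated with the accuracy of nodal staging is the number of lymph nodes analyzed from the operative specimen". A report that fluorescence retrieves nodes missed by classical search would therefore be read as a staging advantage, although the data might show only the value of searching twice.

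**Working it through.** The protocol states no figure for this comparison, so there is nothing to reproduce. The calculations below are illustrations, and assumed inputs are marked.

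**Inputs**

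- Patients: about 34 in the monocentric step (First Step) and about 146 in the multicentric step (Second Step).
- Nodes per specimen: 12, the minimum that the Discussion cites as recommended. It is not an expected yield.
- *m*, the share of nodes missed at first search, and *r*, the share of missed nodes that a plain repeat look recovers: assumed.
- *q*, the share of specimens in which a plain repeat look finds at least one node: assumed.

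**1. Camera no better than a repeat look, counted by node**

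With nodes independent, the expected extra nodes in 34 patients are 34 × 12 × *m* × *r*, and the chance of at least one is 1 − (1 − *mr*)^(12 × 34) = 1 − (1 − *mr*)^408.

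| *m* | *r* | Expected extra nodes | Chance of at least one |
|---|---|---|---|
| any | 0% | 0 | 0% |
| 2% | 10% | 0.8 | 56% |
| 5% | 10% | 2.0 | 87% |
| 5% | 25% | 5.1 | 99% |
| 10% | 25% | 10.2 | >99.9% |

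**2. The same question, counted by specimen**

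The chance of at least one specimen with an extra node is 1 − (1 − *q*)^34 in the monocentric step: 29% at *q* = 1%, 50% at 2%, 83% at 5% and 97% at 10%. With 146 specimens it is 77% at 1% and 95% at 2%.

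**3. Why the extra-node count alone is not a comparison**

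Assume 12 nodes, a classical search that finds 90% of them, a camera that alone would find 30%, and independent detection. Side by side, the camera is worse by 12 × (0.90 − 0.30) = 7.2 nodes per patient. In sequence it adds 12 × (1 − 0.90) × 0.30 = 0.36 nodes per patient. Both figures are correct, but they answer different questions, and only the second corresponds to what the last pass counts.

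**The case against.** The strongest reply is that the pass is described as complementary exploration and that its nodes are named as ones the classical search did not find. The Discussion expects fluorescent nodes to be far fewer than the total resected. Read in that light, the aim means nodes additional to classical search, and for that purpose standard search first and camera second is a legitimate descriptive order. This stands. The fault lies in the comparative wording and in the missing second-look reference, not in the sequence itself.

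A reader might go further and infer that the design can only favour fluorescence. The documents do not support that, for two reasons:

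- Fluorescence also searches first, in the operating room. Nodes that it reveals there carry a green stitch before the pathologist starts and cannot be counted as clinically unfound. That works against fluorescence.
- Unstitched nodes found classically are scored as fluorescent or not, so part of the opposite discordance is collected. It is only part, because a node scored in a cassette has not been shown to be detectable, or undetectable, by camera within the specimen.

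A reader might also infer that the result would be positive even if the camera adds nothing. That is too strong. The count is zero if the last pass recovers nothing, and no threshold defines a positive result. At *q* = 1% the chance of any extra node in 34 specimens is only 29%.

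**Conclusion.** The point holds as a limit on interpretation. The last pass measures the uncontrolled additional yield of a second, camera-assisted search. It cannot attribute that yield to fluorescence and cannot support the statement that fluorescence detects more nodes than classical analysis. Under the assumed rates, a camera no better than a repeat look would have a 56% to 99% chance of showing at least one extra node in 34 patients for miss rates of 2% to 5% and recovery of 10% to 25%. These figures depend on the assumed *m*, *r* and *q*, on 12 nodes per specimen and on independence; the protocol supplies no miss or recovery rate.

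The reach is modest. Node yield is outside the named objectives, and the sensitivity endpoint and the Simon decision rule do not use it. It would be wrong to infer that the main result is compromised. The search order and the stated purpose are nevertheless set in the protocol, and analysis cannot recover a second-look reference that was never recorded.

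**What to change.** In the pathology Fluorescence Imaging section:

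1. Replace the comparative aim with *additional yield of a second, camera-assisted search after classical search*.
2. For each histologically confirmed extra node, record whether it was fluorescent. Non-fluorescent extras give a partial measure of plain second-look yield. It is partial because an unaided second look could also have found some of the fluorescent ones.
3. Report the extra nodes beside two counts: classically found nodes that were not fluorescent, and nodes already green-stitched in the operating room.
4. State that no conclusion will be drawn that fluorescence finds more nodes than classical search.

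The cost is one extra recorded item per node and a more modest claim; no patients or searches are added. Alternating the search order between specimens is optional and not required. By itself it would not isolate the second-look effect, because no specimen would receive an unaided second search after a classical first one.
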